## Abstract

**Background:**

The studies which address the impact of costs of robotic vs. laparoscopic approach on quality of life (cost-effectiveness studies) are scares in general surgery.

**Methods:**

The Spanish national study on cost-effectiveness differences among robotic and laparoscopic surgery (ROBOCOSTES) is designed as a prospective, multicentre, national, observational study. The aim is to determine in which procedures robotic surgery is more cost-effective than laparoscopic surgery. Several surgical operations and patient populations will be evaluated (distal pancreatectomy, gastrectomy, sleeve gastrectomy, inguinal hernioplasty, rectal resection for cancer, Heller cardiomiotomy and Nissen procedure).

**Discussion:**

The results of this study will demonstrate which treatment (laparoscopic or robotic) and in which population is more cost-effective. This study will also assess the impact of previous surgical experience on main outcomes.

## Background

The advantages of minimally invasive approach in general surgery procedures have been reported in many studies (1). Robotic surgery provides three-dimensional vision, seven motion degrees, stable vision, disabling hand's tremor, and a well-established feasibility, safety, and effectiveness profile (1–3).

While randomized controlled trials and observational studies have demonstrated the safety and effectiveness of robotic surgery, they rarely assess its economic impact on the healthcare system compared with the laparoscopic technique (4–7). This needs to be addressed but planning such analyses before starting the study is essential and most of the times was not properly measured.

## Current Evidence

Several studies have shown that robotic-assisted surgery is associated with higher costs than laparoscopy (6–8). Contributing factors include purchasing the robot by the healthcare institution, maintenance costs, disposable materials, and longer operative times. These apply to most general surgery procedures; but some organ- and procedure-specific considerations are needed.

Regarding distal pancreatectomy, two recent meta-analyses aiming to compare the costs of robotic and laparoscopic distal pancreatectomy, demonstrated that the latter seems to contain costs, despite some potential technical advantages of the robotic technique (e.g., decreased conversion rate) (8, 9). However, the surplus cost of robotic distal pancreatectomy resection might be reduced given the decrease in hospitalization costs.

Regarding rectal surgery, six studies in the literature reported on the costs of robotic vs. laparoscopic rectal resection (7, 10–14). According to Morelli et al., hospital costs were slightly higher in the laparoscopic group, whereas higher operative costs were reported in the robotic rectal resection group (11). Baek et al. reported overall costs to be higher in the robotic group, and data on hospitalization costs were found to be generally lacking (13).

Some published result must be interpreted with caution as the analysis is based on heterogeneous data with outcomes conditioned by the lack of an economical standardization of reported costs. A study from 2014 reported that robotic-assisted colorectal resections had higher total ($5,272 increase, *p* < 0.001) and direct costs ($4,432 increase, *p* < 0.001), longer operating time (39 min, *p* < 0.001), and were more frequently associated to postoperative bleeding (OR 1.6, *p* = 0.014) than laparoscopic resections. The data source for this study was a United States national inpatient database evaluating a total of 17,265 laparoscopic and 744 robotic colorectal resections between 2009 and 2011 (10). However, there were some limitations in this study that may have influenced the results. First, the authors used an administrative database which had the possibility of coding errors. Second, many centers were involved, which also suggests a high heterogeneity of the techniques in both the laparoscopic and robotic groups, including the type of devices, the implementation of hybrid vs. totally robotic techniques, the phase of the learning curve, and patient volume at the center. Furthermore, some data were missing, such as the conversion rate.

The main reasons why the costs of robotic approach are poorly reported in the literature are mainly due to the challenge in their calculation. If, from one hand, costs associated with the hardware are easy to obtain, the impact of the surgical procedure on overall costs is difficult to be quantified.

Indeed, overall costs should include not only operative costs but also costs related to the rehabilitation facility, days out of work after surgery and its impact on the quality of life (QoL), which make an exact estimate challenging. Studies which address the impact of costs of a new technique on QoL are named *cost-effectiveness studies*.

## The Rationale for the Study

The current debate about introducing a new technology mainly concerns its cost-effectiveness (15). Only a cost-effectiveness analysis can shed light on uncertainties concerning the economic impact of robotic vs. laparoscopic surgery. However, reliable, prospective, adequately designed cost-effectiveness studies are still lacking (16–21).

QoL after a surgical procedure can be measured through different scores (22). In order to conduct cost-effectiveness studies, QoL needs to be objectively and consistently measured, using validated tools. The most used scores to grade QoL are the generic SF-36 and the EuroQol EQ-5D-5L tests, that can be transformed into QALYs, giving a more objective view of the patient's improvement after the planned treatment (health perspective) (23).

Apart from prospective series, some studies only used a decision-analytic model derived from available literature for costs, QoL and outcomes (24). However, these results must be interpreted with great caution since the insufficient data available in the literature imply a high risk of bias.

According to the pyramid of evidence, randomized clinical trials represent the highest level of study types. However, in a surgical setting of robotic vs. laparoscopic approach, these trials are difficult to be performed (e.g., expensive, ethical issue, blinding) and generalized (strict inclusion criteria) (25). Hence, prospective, adequately designed and conducted non-randomized clinical trials can provide very clinically relevant information.

A well-designed cost-effectiveness study would answer whether its superiority justifies the higher costs of robotics in terms of gained QoL after surgery. This protocol describes the study of nationwide assessment of the cost-effectiveness of the laparoscopic vs. robotic approach, which will define which approach is more convenient for each condition or patient.

## Aims of the Study

### Primary Aim of the Study

To determine if robotic surgery is more cost-effective than laparoscopic surgery in several surgical conditions and patient populations. The present prospective study will evaluate the incremental cost per quality-adjusted life year (QALY) gained from healthcare perspectives.

### Secondary Aims of the Study

The secondary aim is to explore the difference between groups concerning assessment of efficacy (hospital stay, pain, proportion and time to uptake of chemotherapy), and measures of safety (adverse health events).

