## Data Collection

### Clinical Data

Clinicians will be requested to register medical data related to surgery (operation equipment, skin-to-skin operating time, blood loss, surgical equipment, number of surgeons), hospital stay (intensive care unit, high dependency unit, ward), complications and associated management (interventions, additional imaging, additional hospitalization). This data will be entered into an electronic Case Report Form (eCRF) online database (CASTOR).

Complications will be classified according to the Clavien-Dindo classification of surgical complications (26) and registered as adverse or serious adverse events. Participants' overall morbidity will be assessed using the Comprehensive Complication Index (CCI) (27). The 95% confidence intervals (CI) for the difference in the means between the two groups will be reported as a primary result. Since the CCI is approximately normally distributed, the 95% CI can be computed using the normal distribution. Further descriptive measures will be reported in terms of mean and standard deviation.

Missing data will thus be managed depending on the cause of missingness. If missingness may directly or indirectly be related to the treatment, it may cause a bias even in the intention-to-treat analysis. In such a situation, the missing data will be reported in the final report, and missing data in the intention to treat analysis will be analyzed according to the worst-case scenario method (failure).

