## Sample Size Calculation and Statistical Methods

### Sample Size

There are concerns about calculating power and sample size in cost-effectiveness studies (28). Although there is some uncertainty, the Incremental Net Benefit (INB) is a measure that is easier to interpret and work with, since a positive INB means that the new proposed treatment is cost-effective (29). Medicare calculations of power and sample size are calculated against some value of Maximum Willingness to Pay (WTP) for a unit of treatment effect. The WTP is defined from a societal perspective, and, although in Spain there is no specific WTP threshold in healthcare, according to the National Institute for Health Care Excellence (NICE) (30) and Spanish Recommendations on Economic Evaluation of Health Technologies (31) we use a WTP of 20,000 € and 30,000 € per QALY as a threshold, to recognize which treatment is most cost-effective, as follow:

$$\begin{array}{l} \text{INB}=\left[\left(\text{EffectNew-EffectComparatore}\right)*\text{WTP}\right]\\ -\left(\text{CostNew-CostComparator}\right) \end{array}$$

This sample size calculation was realized with consultation of two statisticians.

Considering previous retrospective reports on cost-effectiveness studies (16–21) in which a minimum of 3,000 € for QALY gained was considered cost-effective, assuming a 5% lost-to-follow-up-rate and the two-sided significance level (α) set at 5% and power (1-β) at 80%, a minimum total of 60 patients need to be allocated in each procedure group comparison (30 laparoscopic vs. 30 robotic).

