### Statistical Method

Data will be analyzed using the SPSS statistical program (SPSS Inc. Chicago, IL, USA). In order to compare the means of the quantitative variables when these followed a normal distribution, a variance analysis and Student's *t-*test will be used. For the rest of the variables, both the Mann-Whitney and Kruskal-Wallis tests will be performed. For categorical variables, a Chi-square test will be implemented. Results with a *P*-value lower than 0.05 will be considered statistically significant.

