### Cost-Effectiveness Analysis

The economic evaluation will be performed as cost effectiveness and cost–utility analyses from a healthcare perspective, with a time horizon of 3 months.

The cost–utility endpoint will be the cost per QALY. The results will be reported in accordance with CHEERS guidelines (23). Data will be collected in the early post-operative period of time (3 months from the surgery) in order to capture as much as possible only the QoL mainly related to the surgical approach instead of the issues related to all treatment process (adjuvant treatment, stoma issues, etc.) which patients are dealing with in a later period of time.

An independent company (Institute for Validation of Clinical Efficacy - IVEC) will perform the financial analysis, eliminating the risk of an observer bias.

A model-based cost-utility analysis estimating mean costs and QALYs per patient will be performed. A stochastic cost-utility analysis will be undertaken. The incremental cost-effectiveness ratio (ICER) will be estimated using the overall costs of the robotic and laparoscopic procedures and QALYs derived from patient interviews to find the incremental cost per QALYs gained.

The INB will be calculated to estimate decision-makers maximum willingness to pay (WTP) for a QALY gained. The INB will be calculated as the mean QALYs per patient multiplied by WTP threshold minus the mean cost per patient for the treatment. The decision rule is to adopt the treatment if the INB > 0, and the alternative with the highest INB represents best value for money.

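### Time to uptake of chemotherapy is left to tests for fully observed values, so the time comparison is likely to rest on starters only and understate a timing difference (minor)

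*Protocol article*

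**What the plan says.** - **Outcome.** Secondary Aims of the Study names "proportion and time to uptake of chemotherapy" as one of the efficacy measures. The status is exploratory: "The secondary aim is to explore the difference between groups concerning assessment of efficacy".
- **Tests.** Statistical Method covers three kinds of variable. ANOVA and Student's t-test are to be used "In order to compare the means of the quantitative variables when these followed a normal distribution". Then: "For the rest of the variables, both the Mann-Whitney and Kruskal-Wallis tests will be performed". Finally: "For categorical variables, a Chi-square test will be implemented". No method for censored times is named.
- **Observation period.** Cost-Effectiveness Analysis says: "Data will be collected in the early post-operative period of time (3 months from the surgery". The reason given there is to keep out issues of later treatment, with adjuvant treatment as an example. Under Questionnaires, the last contact is also at 3 months. No longer follow-up is stated.
- **Missing data.** Under Clinical Data, where missingness may be related to treatment, "missing data in the intention to treat analysis will be analyzed according to the worst-case scenario method (failure".

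**The concern.** Time to chemotherapy is a time-to-event outcome with a cut-off. A patient who starts after the cut-off, never starts, or dies first has no number to enter into a t-test. Such a patient enters a rank test only if a rule says where to rank them. Without a rule, the usual practice is to analyse the recorded times, which means starters only.

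Starting chemotherapy depends on recovery from the operation being compared. A mean or rank among starters therefore conditions on a consequence of the surgery. The slower arm loses its late starters at the cut-off, which pulls its average down towards that of the faster arm. The time result could then suggest little difference in timing when a real one exists, and it would be reported as a separate efficacy result.

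**Working it through.** **The plan's own figure.** The protocol gives no uptake rate, start time or power for this outcome. Its sample size (30 per arm per procedure) concerns the primary outcome; I borrow the 30 only as an assumption. All inputs below are assumed.

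**1. Bias in the starter mean.** Suppose starts occur no earlier than day 21 and are exponential afterwards, with observation to day 90 (a window of 69 days). For median m:

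- scale 1/λ = (m − 21)/ln 2
- not started by day 90: q = exp(−69λ)
- mean among starters = 21 + 1/λ − 69·q/(1 − q)

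| True median | 1/λ | Started by day 90 | Mean among starters |
|---|---|---|---|
| 45 d | 34.6 | 86% | 21 + 34.6 − 69 × 0.136/0.864 = 44.7 d |
| 60 d | 56.3 | 71% | 21 + 56.3 − 69 × 0.293/0.707 = 48.6 d |
| 75 d | 77.9 | 59% | 21 + 77.9 − 69 × 0.412/0.588 = 50.5 d |

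A 15-day difference in medians (60 vs 45) appears as 48.6 − 44.7 = 3.9 days among starters. A 30-day difference (75 vs 45) appears as 50.5 − 44.7 = 5.8 days.

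**2. Power under the same model.** 30 indicated patients per arm, two-sided 5%, simulated several times with 2,000 to 4,000 trials each; ranges show the spread between runs.

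| Analysis | Medians 60 vs 45 | Medians 75 vs 45 |
|---|---|---|
| Mann-Whitney, starters only | 9–11% | 15–16% |
| Chi-square on proportion started | 30–32% | 68–71% |
| Mann-Whitney, non-starters ranked last | 32–33% | 69–71% |
| Log-rank, all patients | 38–41% | 76–79% |

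**3. A different model.** Some patients never start; the others have log-normal times (log-SD 0.4). 30 per arm, 90-day horizon, 3,000 trials.

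| Ever start; median | Starters only | Ranked last | Chi-square |
|---|---|---|---|
| 60% vs 60%; 50 vs 50 d (no difference) | 4.9% | 5.6% | 5.1% |
| 50% vs 80%; 50 vs 50 d | 4.5% | 48% | 61% |
| 80% vs 80%; 60 vs 42 d | 68% | 60% | 14% |
| 80% vs 80%; 100 vs 60 d | 49% | 94% | 84% |
| 60% vs 80%; 60 vs 45 d | 42% | 80% | 56% |

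The second row is a pure difference in uptake: the starters-only test misses it and chi-square finds it. In the third row most starts fall inside the window, and the starters-only test loses nothing. In the fourth row many starts fall after day 90. The starters-only test then loses about half its power, and a 40-day difference in medians appears as a mean difference of 13 days.

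**The case against.** **Exclusion is not written down.** A reader might infer that the plan removes non-starters. It does not say so. Mann-Whitney on a common 90-day horizon with non-starters ranked last is valid (5.6% rejection under no difference), and in step 2 its power comes close to log-rank. This stands: naming Mann-Whitney is not itself the error. But the plan does not state that ranking, and it cannot serve the t-test branch, which needs a numeric time for everyone.

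**The proportion is a co-listed outcome.** A reader might conclude that a difference between approaches would be hidden, or even reversed. Chi-square on the proportion counts every non-starter and recovers much of the signal, so hidden is too strong. None of the scenarios shows a reversal. What remains distorted is the separately reported time comparison.

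**The worst-case rule may cover it.** It points towards counting such patients as failures. However, it is written for missing data. A patient followed for 3 months without starting is censored, and failure is not a value on a time scale.

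**The 3-month limit appears under the economic analysis.** True, and its use for chemotherapy dates is probable rather than explicit. No longer period is given elsewhere.

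**The article is condensed, and detail may sit in a document not shown.** This holds for detailed censoring rules. The point rests on what is stated: a general test scheme that sends all remaining variables to rank tests.

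**Thirty indicated patients per arm is optimistic.** This stands. Only some patients in the cancer procedures would have an indication. With an illustrative 10 per arm, even log-rank has only about 15–17% power (60 vs 45 days) or 34% (75 vs 45 days).

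**Conclusion.** The point holds as a mismatch between outcome and method. The tests stated for non-categorical outcomes do not suit a start time that is unobserved for anyone who has not begun chemotherapy by 3 months. In their usual use they limit the comparison to starters and tend to understate a timing difference when starts run past the window.

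Under the step 1 assumptions, a 15-day difference in medians shows as about 4 days among starters, with power of about 10% against about 40% for log-rank. The size depends on uptake rates and timing that the documents do not give, and it is small if nearly all starts fall within 90 days. Priority is minor: the outcome is exploratory, and the primary cost-effectiveness analysis, its sample size and its decision rule are unaffected.

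**What to change.** Add one or two sentences to Statistical Method:

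- Define the denominator as patients with an indication for adjuvant chemotherapy.
- Analyse time from surgery to first chemotherapy by cumulative incidence, censored at 3 months or last contact, with death before start as a competing event.
- Compare the approaches by log-rank or Cox. At the least, use Mann-Whitney with non-starters ranked last on a common 3-month horizon.
- Keep the chi-square test for the proportion started by 3 months, on the same denominator.
- State that the 3-month window applies to this outcome, if that is intended.

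The cost is a short text change. It uses the same start dates plus the date of death or last contact, and adds no patients or visits.

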## Study Design

The Spanish national study on cost-effectiveness differences among robotic and laparoscopic surgery (ROBOCOSTES) is designed as a prospective, multicentre, national, observational study conducted in Spain between the 15th of January and the 15th of December 2022.

### Study Population

Patients are considered eligible to enter the study if they meet the following inclusion criteria:

1. Adults aged ≥18 years of age.

2. Consecutive patients undergoing: distal pancreatectomy, gastrectomy (total and subtotal), sleeve gastrectomy, inguinal hernioplasty with mesh, rectal resection for cancer, Heller cardiomiotomy and Nissen procedure.

3. Type of disease approachable by both laparoscopic and robotic minimal access surgery.

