## Methods for Minimizing Bias

The number of patients screened, the number included, and those analyzed will be reported, and differences will be explained. In addition, the patient flow and the Consolidated Standards of Reporting Trials (CONSORT) flowchart will be reported in the final analysis (32).

In addition, analysis will be stratified according to each surgeon's previous experience before starting the study, type of hospital (public, university) and total number of beds.

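### Gastrectomy pools total and subtotal resections in a non-randomised comparison, and the stated analysis does not adjust for extent of resection

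*Protocol article*

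**What the plan says.** The abstract (Methods) states the purpose by procedure: "The aim is to determine in which procedures robotic surgery is more cost-effective than laparoscopic surgery". It names seven procedures, with gastrectomy counted once: "distal pancreatectomy, gastrectomy, sleeve gastrectomy, inguinal hernioplasty, rectal resection for cancer, Heller cardiomiotomy and Nissen procedure". The eligibility list under Study Population shows that this one entry covers two operations: "gastrectomy (total and subtotal), sleeve gastrectomy, inguinal hernioplasty with mesh, rectal resection for cancer".

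Sample Size sets the size of each comparison: "a minimum total of 60 patients need to be allocated in each procedure group comparison (30 laparoscopic vs. 30 robotic"). No section enumerates the procedure groups beyond these lists.

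Study Design describes a "prospective, multicentre, national, observational study conducted in Spain", so the approach is not assigned at random.

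Methods for Minimizing Bias stratifies the analysis by each surgeon's earlier experience, and by "type of hospital (public, university) and total number of beds". Statistical Method names group comparisons without covariates (t-test, analysis of variance, rank tests, chi-square). Cost-Effectiveness Analysis forms the ICER and INB from mean costs and QALYs by approach. None of these sections mentions extent of gastric resection.

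**The concern.** The three strata describe the surgeon and the hospital. None describes the operation done within the gastrectomy group. Without randomisation, nothing in the design makes the share of total gastrectomies equal in the robotic and laparoscopic arms. If the shares differ systematically, and total and subtotal gastrectomy differ in cost or QALYs, part of the robotic-minus-laparoscopic difference is a total-minus-subtotal difference.

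The adoption rule is an INB above zero, so a shift in the mean can change the gastrectomy verdict. The planned 5,000 Monte Carlo simulations would not reveal this as described: they spread uncertainty around the input means and do not correct a mean that is confounded. One of the seven comparisons is affected.

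**Working it through.** **1. The plan's own figure.** The 30 per arm cannot be reproduced, because no standard deviation is given. It can only be solved backwards. This requires reading the phrase "a minimum of 3,000 € for QALY gained was considered cost-effective" as a difference of 3,000 €, which is an assumption. With two-sided α = 0.05 and power 0.80:

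- n per arm = 2 × (1.96 + 0.84)² × (SD / 3,000)².
- SD = 4,000 € gives 28 evaluable, and 28 / 0.95 = 29.5, rounded up to 30.

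An SD of about 4,000 € is therefore what 30 per arm would imply. It is used below only as a scale for noise.

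**2. Size of the confounding.** Let Δp be the difference between arms in the share of total gastrectomies, D the total-minus-subtotal cost gap and Q the QALY loss of total relative to subtotal. Then

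spurious INB difference = Δp × (D + WTP × Q).

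Only the WTP values (20,000 and 30,000 € per QALY) come from the protocol. The rest are assumptions: Δp 0.10–0.30, D 2,000–4,000 €, Q 0.01–0.02 over 3 months.

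| Part | Low end | High end |
|---|---|---|
| Cost | 0.10 × 2,000 = 200 € | 0.30 × 4,000 = 1,200 € |
| QALY | 0.10 × 0.01 × 20,000 = 20 € | 0.30 × 0.02 × 30,000 = 180 € |
| Sum | 220 € | 1,380 € |

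The parts add only if total gastrectomy both costs more and yields fewer QALYs. The sign depends on which arm holds more total gastrectomies, which is unknown.

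**3. Against the decision scale.** At the protocol's thresholds, a gain of 0.01 QALY is worth 0.01 × 20,000 = 200 € to 0.01 × 30,000 = 300 €. The 0.01 is an illustrative choice.

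**4. Against sampling noise.** With an SD of 4,000 € and 30 × 0.95 = 28.5 evaluable per arm, SE = 4,000 × √(2 / 28.5) ≈ 1,060 €. If there is no true difference, the two-sided error of a nominal 5% test becomes:

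| Systematic shift | Two-sided error |
|---|---|
| 200 € | 5.4% |
| 400 € | 6.6% |
| 600 € | 8.7% |
| 1,200 € | about 20% |
| 1,380 € | about 26% |

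Most of the range is small against noise. The last two rows need the extreme assumptions.

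**5. Chance imbalance.** If both arms had the same true share of 40% (assumed), two Binomial(30, 0.4) draws differ by at least 10 points with probability 0.51 and by at least 20 points with probability 0.147. This is sampling error, which averages to zero over repeated studies, so it is not bias. It does add variance that adjustment can remove. With a within-type SD of 4,000 €, the between-type variance is 0.4 × 0.6 × D². For D = 2,000 this is 0.96 million of 16.96 million (about 6%). For D = 4,000 it is 3.84 million of 19.84 million (about 19%).

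**6. Can extent be crossed with the existing strata?** At 40%, each arm holds about 0.4 × 30 = 12 total gastrectomies. If each of the three existing strata had only two levels, there would be 2 × 2 × 2 = 8 cells. Extent would make 16, or 60 / 16 = 3.75 patients per cell over both arms. That is not workable.

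**The case against.** The best case against the point is that it rests on inference and silence. Study Population is an eligibility list, not a definition of analysis sets, and the single pooled group is inferred. A pooled gastrectomy estimate is a legitimate, broader question. Methods for Minimizing Bias does not say that its strata are exhaustive, and a full protocol or analysis plan, not shown, may adjust for case mix. Extent of resection is also one example of a wider matter: no patient-level or disease-level confounder is among the strata.

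Much of this stands, and it limits the point. But no section suggests that the two operations are analysed apart. The article does commit to a list of strata under a bias heading, and that list leaves out a distinction that its own eligibility wording makes. Wanting a pooled estimate does not remove the need to compare like mixes.

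Three stronger readings are tempting and are not supported:

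- A reader might take the high probability of chance imbalance as proof of bias. It shows only imprecision, and nothing in the documents says that the choice of approach depends on extent of resection.
- A reader might infer from the separate listing of sleeve gastrectomy that the protocol concedes that total and subtotal gastrectomy need their own comparisons. The listing shows only that sleeve gastrectomy is a separate group. The bracketed wording suggests that the pooling of the other two is deliberate.
- A reader might treat the euro figures as an estimate of the error. Every clinical input to them is assumed.

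**Conclusion.** The point holds in a limited form. As described, the gastrectomy comparison takes no account of extent of resection, and the design does not balance it. The gastrectomy ICER and INB are confounded if two conditions both hold: the share of total gastrectomies differs systematically between approaches, and the two operations differ in cost or QALYs. The documents establish neither, so size and direction are unknown. The illustrative shift of 200–1,200 € from costs is only a conditional range, and its lower part is minor beside a standard error of about 1,060 €, itself based on a back-solved SD. The conclusion also assumes that gastrectomy is one 30-versus-30 group. It does not follow that the gastrectomy result will be wrong, or that the group must be split in two. The change is worth making because it is cheap and protects one of the seven primary comparisons.

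**What to change.** In Methods for Minimizing Bias, add that the gastrectomy comparison of cost, QALYs and INB will be adjusted for extent of resection (total or subtotal). Either of two forms will do: one covariate in the model, or robotic-minus-laparoscopic differences within each type, averaged with weights equal to the type shares in the whole gastrectomy sample. Do not cross extent with the surgeon and hospital strata. Report the within-type estimates as descriptive only.

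Confirm that the eCRF records which operation was done. The Clinical Data section does not list it among the recorded items, and a patient can be eligible under the gastrectomy entry without the type being noted.

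Cost: a sentence or two in the analysis text, one degree of freedom, imprecise within-type estimates, and possibly one eCRF field.
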